### **7.10 Asthma History Questionnaire**

The asthma history questionnaire will be completed at the baseline visit in asthmatic subjects only, to provide details of the subject’s asthma history. The questionnaire will be provided in paper format to the study centers.

### **7.11 Safety Evaluations**

Any procedure related clinically significant abnormalities persisting at the end of the study will be followed by the investigator until resolution or until a clinically stable endpoint is reached.

The study will include the following evaluations of safety and tolerability according to the time points provided in the Schedule of Events.

#### **Adverse Events**

Adverse events will be reported by the subject for the duration of the study. Adverse events will be followed by the investigator as specified in Section 10, Adverse Event Reporting.

#### **Clinical Laboratory Tests**

Blood samples for serum chemistry and hematology will be collected at screening and can be repeated if medically necessary during the study. The list of analyses to be completed is in [Attachment 2](#). In addition to serum chemistry and hematology, the following assessments will also be performed:

- Urine Pregnancy Testing for all women participating in the study.
- Serology (HIV-1 antibodies, HBsAg, and anti-HCV antibodies).
- Urine Drug Screen (amphetamine, barbiturates, benzodiazepines, cannabinoids, cocaine, methadone, opiates, tricyclic antidepressants).
- Urine cotinine test.
- Alcohol breath test.

#### **Electrocardiogram (ECG)**

12-lead ECGs will be recorded at a paper speed of 25 mm per second until 4 regular consecutive complexes are available. The PI will review the ECG to ensure that there is no abnormality which would place the subject at risk from participation in the study.

#### **Vital Signs**

Measurement of supine vital signs (resting pulse rate, blood pressure, and temperature) will be performed after 10 minutes of rest at the timepoints specified in the study schedule of events (see [Attachment 1](#)). When scheduled concurrently with a blood draw or ECG, vital signs should be measured after the ECG and before the blood draw.

If any clinically significant changes in vital signs are noted and considered related to study procedures, they must be reported as AEs (see Section 10) and followed to resolution, or until reaching a clinically stable endpoint.

A detailed listing of vital signs to be evaluated will be provided in the Study Reference Manual.

### **Physical Examination**

Physical examinations will be performed by the investigator or designated physician. The timepoints of these examinations are specified in the Schedule of Events (see [Attachment 1](#)).

Any abnormalities or changes in severity noted during the review of body systems should be documented in the source document and recorded on the CRF.

A new, clinically significant finding (in the opinion of the investigator) not noted at screening, and considered related to study procedures, must be captured as an AE (see Section 10). In addition, resolution of any abnormal findings during the study will be noted in the source document and in the CRF.

A detailed listing of body systems to be evaluated for initial physical exam and subsequent brief physical exams will be provided in the Study Reference Manual.

## **7.12 Genomic Evaluation**

There are 2 parts to the genomic component of this study.

Subjects will be given the option to participate in Part 1 only, Part 2 only, both parts, or neither part of the genomic component of this study (where local regulations permit).

### **Analysis Related to the Study (Part 1)**

Collection of genomic samples will allow for genetic research to help understand asthma. Genetic analysis will be conducted if it is hypothesized that this may help resolve issues with the clinical data. DNA samples will only be used for genetic research related to asthma. Genetic research may consist of the analysis of 1 or more candidate genes or of the analysis of genetic markers throughout the genome (as appropriate) in relation to asthma clinical endpoints. Subjects will be offered the separate option to consent to storage of their optional samples for future research as scientific discoveries are made.

### **DNA Storage for Future Research (Part 2)**

Part 2 of the genomic research allows for the storage of DNA samples for future genetic research related to asthma. DNA samples will be stored for up to 5 years after the study is complete. Stored DNA samples and relevant clinical data will be de-identified after the Clinical Study Report has been issued. This involves removing personal identifiers and replacing the study subject identifier with a new number to limit the possibility of linking genetic data to a subject's identity.

Refusal to participate in genomics testing will not result in ineligibility for participation in the rest of the clinical study. Further, a subject may withdraw genomic consent at any time without affecting their participation in other aspects of the study.

## **8 SUBJECT COMPLETION/WITHDRAWAL**

### **8.1 Completion**

A healthy subject will be considered to have completed the study if he or she has completed the bronchoscopy procedure and telephone follow-ups on the day following bronchoscopy and 1 week after bronchoscopy. Asthmatic subjects will be considered to have completed the study if he or she completes the final biomarker visit. Subjects who prematurely discontinue study participation for any reason before completion of their final visit will not be considered to have completed the study.

### **8.2 Withdrawal From the Study**

A subject will be withdrawn from the study for any of the following reasons:

- Lost to follow-up.
- Withdrawal of consent.
- Death.
- The investigator believes that for safety reasons (eg, adverse event) it is in the best interest of the subject to stop participation.
- The subject becomes pregnant.
- The study investigator or Sponsor for any reason stops the study or stops the subject's participation in the study.

Subjects who terminate study participation before their last scheduled visit should contact the investigational site if possible for a final visit. The Study coordinator should consult with the Sponsor as to what testing should be performed at that visit.

In the event a subject is lost to follow-up, every possible effort must be made by the study site personnel to contact the subject and determine the reason for discontinuation/withdrawal. The measures taken to follow up with a subject must be documented.

When a subject withdraws before completing the study, the reason for withdrawal is to be documented in the CRF and in the source document. Those subjects chosen to undergo bronchoscopy who withdraw prior to the bronchoscopy will be replaced with new subjects until up to 30 subjects from each subject category (healthy, mild, moderate or severe asthma) have undergone a bronchoscopy. Subjects who withdraw from the longitudinal sample collection portion of the study will not be replaced.

A subject who withdraws from the main part of the study will have the following options regarding genomic research:

- The DNA extracted from the subject's blood will be retained and used in accordance with the subject's original genomic informed consent.
- The subject may withdraw consent for genomic research, in which case the DNA sample will be destroyed and no further testing will take place. To initiate the sample destruction process, the investigator must notify the sponsor site contact to request sample destruction. The sponsor site contact will, in turn, contact the genomics representative to execute sample destruction. If requested, the investigator will receive written confirmation from the sponsor that the sample has been destroyed.

### **Withdrawal From Genomic Research Only**

The subject may withdraw consent for genomic research while remaining in the clinical study. In such a case, any DNA extracted from the subject's blood will be destroyed. The sample destruction process will proceed as described above. However, all samples will be made nonidentifiable after the clinical study report is issued and thereafter cannot be identified for destruction. If the sample has already undergone conversion to the nonidentifiable format, the sponsor will notify the investigator in writing.

## **9 STATISTICAL METHODS**

No formal hypothesis testing will be conducted. Data will be summarized using descriptive statistics. Continuous variables will be summarized using the number of observations, mean, SD, minimum, median, and maximum values as appropriate. Categorical values will be summarized using the number of observations and percentages as appropriate.

### **9.1 Subject Information**

For all subjects who are enrolled in this study, descriptive statistics of demographic information and baseline characteristics will be provided.

### **9.2 Sample Size**

This is an exploratory study. Therefore, no formal hypothesis is to be tested and no formal power calculation is performed in sample size determination.

The primary objective of this study is to explore asthma-associated biomarkers to aid in the evaluation of new and existing therapeutics for asthma and to understand the correlation between non-clinical models of disease and human disease. To perform this analysis, four groups are required: 3 asthma severity groups of subjects (mild, moderate, and severe) and a healthy control group.

The 3 asthma severity groups are required to:

- Identify biomarkers differentially expressed in asthmatics compared to healthy controls.
- Identify biomarkers differentially expressed among asthma severities.
- Identify subsets of asthmatics defined by biomarker expression profiles.

The healthy control group is required to:

- Identify biomarkers differentially expressed in asthmatics compared to healthy controls.
- Determine whether a biomarker profile expressed by a subset of asthmatics is specific for asthma or is also found in the healthy control population.

To estimate a suitable sample size of subjects to undergo bronchoscopy, the following was considered.

Based upon prior microarray data studies ([Woodruff et al, 2007](#); [Woodruff et al, 2009](#)) and a previous clinical study of golimumab in subjects with asthma (unpublished results), the following assumptions can be made for determining the sample size:

1. Subsets comprising 20% of asthmatics and healthy controls can be identified from gene expression microarray analysis. A 20% subset is considered practical for targeting in personalized/stratified medicine approaches in asthma.
2. A minimum of 5 subjects would be necessary to be able to identify a biomarker-defined subset from hierarchical clustering analysis of gene expression microarray data.

Based on these assumptions, bronchoscopy samples from 25 subjects each for the 4 groups are needed to identify biomarker-defined subsets comprising at least 20% of subjects within a group. Assuming that samples adequate for analysis would be obtainable from 80% of subjects, a sample size of 30 subjects per group undergoing bronchoscopy is needed.

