## **STATISTICAL METHODS**

No formal hypothesis testing will be conducted. Data will be summarized using descriptive statistics. Continuous variables will be summarized using the number of observations, mean, standard deviation (SD), minimum, median, and maximum values as appropriate. Categorical values will be summarized using the number of observations and percentages as appropriate.

Sample sizes of 50 subjects per asthma severity group and 30 healthy subjects were chosen based on previous experience with microarray datasets. The power and effect size to detect differential expression between asthma severity groups and the control group and among the asthma severity groups was evaluated. The proposed sample size will appropriately generate descriptive measures on exploratory biomarkers.

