The second interim analysis will be conducted upon completion of last bronchoscopy procedures in the last subject participating in the bronchoscopy portion of the study. The main goal of this interim analysis will be biomarker evaluation of the samples collected at the screening, baseline, and bronchoscopy visits and will include but will not be limited to microarray analysis of RNA isolated from samples and soluble analyte analysis of serum and IS samples. To support this analysis a data base lock will be performed to provide demographic and clinical information for the planned biomarker analyses. The output of this interim analysis will include, but not be limited to, study population results, safety results, information on asthma characteristics of mild, moderate and severe cohorts and their respective clinical parameters, differences in biomarkers across cohorts, identification of biomarker-defined subsets across and within cohorts, correlations of biomarker, clinical, and demographic parameters, and correlations of biomarker measurements across sampling matrices.

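### Section 9.2 sizes the bronchoscopy groups on an expected count: with 25 samples, a true 20% subset has only a 58% chance of supplying the 5 members the plan requires

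*Protocol*

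**What the plan says.** Protocol Section 9.2 builds the bronchoscopy sample size from two assumptions. The first is that "Subsets comprising 20% of asthmatics and healthy controls can be identified from gene expression microarray analysis"; the same item justifies 20% as a practical size for targeting in stratified medicine. The second is that "A minimum of 5 subjects would be necessary to be able to identify a biomarker-defined subset from hierarchical clustering analysis".

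From these two it concludes that "bronchoscopy samples from 25 subjects each for the 4 groups are needed to identify biomarker-defined subsets comprising at least 20% of subjects", and the sentence goes on to place those subsets inside a single group. An allowance for unusable samples follows: "Assuming that samples adequate for analysis would be obtainable from 80% of subjects, a sample size of 30 subjects per group undergoing bronchoscopy" is needed.

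Section 9.2 also says that "no formal hypothesis is to be tested and no formal power calculation is performed in sample size determination". Section 9.3 lists among the outputs of the second interim analysis the "identification of biomarker-defined subsets across and within cohorts". The Statistical Methods part of the Synopsis says of enrolment (50 per severity group and 30 healthy subjects) that "The power and effect size to detect differential expression between asthma severity groups and the control group", and among the severity groups, was evaluated.

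**The concern.** No probability stands behind the figure of 25. It makes the average number of subset members equal to the smallest number the plan regards as workable, with no margin for chance. A sample of 25 from a group in which 20% carry a given profile will often contain 4 or fewer carriers, and by the plan's own second assumption the subset then could not be identified.

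This argument sets how many people in each group undergo a research bronchoscopy. It also tells the reader of the eventual biomarker report what a within-cohort clustering result can bear. Someone who takes 9.2 at its word could give an empty result in one cohort more weight than the design supports.

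**Working it through.** **Inputs, all from Protocol Section 9.2**
- Subset prevalence p = 0.20
- Minimum members for clustering = 5
- Evaluable samples per group n = 25
- Share of subjects with adequate samples = 0.80
- Bronchoscopies per group = 30

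No target probability is given.

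**Step 1. The plan's own figure.** Minimum / prevalence = 5 / 0.20 = 25. This reproduces the stated number exactly. Equivalently, the expected count is 25 x 0.20 = 5.

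**Step 2. Chance of at least 5 members with 25 samples.** The count X is binomial (25, 0.20), and P(X >= 5) = 1 - [P(0) + P(1) + P(2) + P(3) + P(4)].

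= 1 - (0.0038 + 0.0236 + 0.0708 + 0.1358 + 0.1867) = 1 - 0.4207 = **0.579**

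The minimum is missed about 42% of the time.

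**Step 3. The same with 30 bronchoscopies.** 30 x 0.80 = 24 evaluable samples, one fewer than 25.
- Exactly 24 evaluable: P(Bin(24, 0.20) >= 5) = 0.540.
- Adequacy random and unrelated to subset membership: each subject contributes an evaluable member with probability 0.80 x 0.20 = 0.16, and P(Bin(30, 0.16) >= 5) = 0.537.

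**Step 4. Larger subsets.** The claim covers subsets of 20% or more, so 20% is its hardest case. With 25 samples:

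| Prevalence in the group | P(at least 5 of 25) |
|---|---|
| 20% | 0.579 |
| 25% | 0.786 |
| 30% | 0.910 |

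**Step 5. Subset size that 30 bronchoscopies support.** Solve P(Bin(30, 0.80 x f) >= 5) = target for f. A target of 80% gives f = 0.267; a target of 90% gives f = 0.311. Both targets are my assumption, since the protocol sets none.

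**Step 6. Clustering across the asthma cohorts.** Pooled evaluable samples: 3 x 24 = 72.
- Subset is 20% of every asthma cohort: P(Bin(72, 0.20) >= 5) = 0.999.
- Subset is 20% of one cohort and absent from the other two: pooled prevalence is 0.20 / 3 = 0.067, and P(Bin(72, 0.067) >= 5) = 0.53. Fixing 24 samples from that cohort gives 0.540, as in Step 3. Pooling gains nothing here.

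Having 5 members present is necessary under the plan's second assumption, but it does not guarantee that clustering will separate them. The probabilities are therefore upper limits on the chance of identification.

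**The case against.** **Exploratory study.** The protocol disclaims hypothesis tests and formal power, and no passage says that an empty cluster result will be read as absence. That limits the weight of the point. It does not make the capability stated in 9.2 correct.

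**A resolution limit.** One could read 20% as an observed share: 5 of 25 analysed subjects is 20% by definition. The first assumption does not fit that reading. It words 20% as a share of asthmatics and healthy controls and defends it as a size worth targeting, which is a statement about populations.

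**The lower edge.** The 58% applies only at exactly 20%, as Step 4 shows. The subgroups described in Section 1.1 (Th2-high and Th2-low) are far larger; at 50% prevalence, 25 samples give a probability above 0.999. This stands, and the restated sentence should show the range.

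**Joint figures.** A reader might infer that a 20% subset must reach 5 members in all three asthma cohorts (0.579^3 = 0.194) or in all four groups (0.579^4 = 0.113). The protocol states no such requirement. On the same assumptions, at least one of the three asthma cohorts reaches 5 with probability 1 - 0.421^3 = 0.93.

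**The driving hypothesis.** A reader might also infer that the shortfall undermines the study's underlying hypothesis. That hypothesis concerns subpopulations of asthma, not of each severity cohort, and for a subset common to the cohorts the across-cohort analysis is ample. Nor does the control group have to yield its own 5-member cluster to serve its stated purpose of checking whether a profile found in asthmatics also occurs in healthy subjects. If 20% of controls carry it, at least one carrier among 24 appears with probability 1 - 0.8^24 = 0.995.

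**The Synopsis.** Its power statement concerns differential expression and total enrolment, so it neither supports nor contradicts the subset count. Its tension with 9.2 is a separate matter of wording.

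**Conclusion.** The point holds for the within-group statement in Section 9.2. The number 25 equates an expected count with a required minimum. At the 20% boundary it gives 58% per group, or about 54% with the planned 30 bronchoscopies and 80% yield. This rests on exact binomial sampling, prevalence of exactly 20% in the group, the protocol's own minimum of 5 and, for the 54%, sample adequacy unrelated to subset membership. The shortfall is smaller for larger subsets and disappears across the asthma cohorts when all of them share the subset; it remains for a subset confined to one cohort.

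Pooling has a limit of its own. Section 4.1 and Table A.2 define the cohorts partly by controller therapy, from none in the mild group to high-dose inhaled corticosteroid in the severe group, so pooled clusters may track treatment rather than disease biology.

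This is an overstated capability in an exploratory rationale. It is worth correcting because it sets the number of bronchoscopies and frames how within-cohort results are read. It does not show that the study is unable to meet its objective.

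**What to change.** 1. **Section 9.2.** Replace the sentence on 25 samples with the per-group probabilities: for a 20% subset, 58% with 25 evaluable samples and about 54% with 30 bronchoscopies at 80% yield; with 25 samples, 79% at 25% prevalence and 91% at 30%. Add that, with 30 bronchoscopies at 80% yield, a subset must be about 27% of a group for an 80% chance of at least 5 members, or about 31% for a 90% chance, and label those targets as chosen for illustration.
2. **Interpretation.** State that finding no cluster within one cohort is not evidence that a 20% subset is absent from it.
3. **Section 9.3.** Note that clustering across cohorts covers a 20% subset common to all asthma cohorts (0.999 with 72 samples) but not one confined to a single cohort (about 0.53). Show cohort and controller treatment alongside any pooled clusters.
4. **Synopsis.** Reconcile the statement that power and effect size for differential expression were evaluated with the statement in 9.2 that no formal power calculation was performed: either report that evaluation or remove the sentence. Subset-count figures should not be put in its place, because they answer a different question.

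The cost is wording only, with no added subjects, procedures or analyses. The stated within-group capability becomes more modest.

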### **3 OVERVIEW OF STUDY DESIGN**

Approximately 180 subjects will be enrolled with up to 50 subjects in each of the mild, moderate and severe asthma cohorts and 30 subjects in the healthy subject cohort. There is no study related therapeutic intervention and this protocol will not restrict or introduce any therapeutic interventions including medications. All subjects will continue to be managed by their personal physicians.

All eligible subjects will be enrolled during screening visits and then undergo the study procedures which will include medical history and physical exam, patient reported outcomes and questionnaires for asthmatic subjects only, pulmonary function testing (PFT), assessment of airway reactivity, blood for routine laboratory tests, biomarkers and DNA evaluation (in consenting subjects), induced sputum collection and exhaled nitric oxide collection. A bronchoscopy will be performed on up to 30 healthy subjects and on up to 30 asthma subjects from each of the asthma severity cohorts. The healthy subject cohort will be evenly split into two age ranges of 18 to 36 years of age or 37 to 55 years of age. All subjects with asthma will have 3 subsequent visits at 3, 6 and 12 months after the baseline visit for repeat sample collection (PFT, exhaled nitric oxide (NO), blood, urine and sputum only) to evaluate stability of phenotypes. The overall study schema is provided in Figure 1.

Two database locks are planned: an interim database lock after completion of the last bronchoscopy procedures for the last subject receiving a bronchoscopy; a second database lock will occur at the end of the study after the last scheduled visit has occurred for the last subject in the study.

[figure not shown]

 30 subjects from each asthma severity group and 30 healthy subjects, within 5-14 days after baseline

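### At the assumed 80% adequacy, 30 bronchoscopies per group are expected to give 24 adequate samples, one short of the 25 that Section 9.2 requires

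*Protocol*

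**What the plan says.** Section 9.2 of the protocol derives the number of bronchoscopies from two assumptions and one allowance for loss.

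- Subset size: "Subsets comprising 20% of asthmatics and healthy controls can be identified from gene expression microarray analysis".
- Smallest usable cluster: "A minimum of 5 subjects would be necessary to be able to identify a biomarker-defined subset" by hierarchical clustering.
- From these two: "bronchoscopy samples from 25 subjects each for the 4 groups are needed".
- Allowance for loss: the section concludes that, with adequate samples "obtainable from 80% of subjects, a sample size of 30 subjects per group undergoing bronchoscopy is needed".

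Section 3 treats 30 as an upper limit: "A bronchoscopy will be performed on up to 30 healthy subjects and on up to 30 asthma subjects" in each severity cohort. Section 8.2 covers subjects chosen for bronchoscopy who withdraw before it. They "will be replaced with new subjects until up to 30 subjects from each subject category" have had the procedure. Section 4.1 gives the same replacement rule without the limit. No section replaces a subject who has the bronchoscopy but gives an unusable sample.

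**The concern.** The section sets a requirement (25 adequate samples), an expected yield (80%) and a number to perform (30), and the three do not agree. Thirty procedures at 80% give 24 usable samples on average.

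This is the only sample size that the protocol works out step by step. It supports one of the stated reasons for having the groups, which is to find subsets defined by biomarker profile. It also justifies the number of subjects who undergo an invasive procedure, so the justification should agree with its own inputs. At stake is whether the design delivers the property claimed for it: 25 usable samples per group, and hence 5 expected members of a 20% subset. No test, error rate or decision rule depends on that figure.

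**Working it through.** **Inputs (all from Section 9.2):** subset share 20%; minimum cluster 5; required adequate samples 25; adequacy 80%; stated bronchoscopies per group 30.

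**Step 1. The protocol's own figures.**
- Required adequate samples: 5 / 0.20 = 25. This matches the protocol.
- Stated bronchoscopies: 25 x 1.2 = 30 reproduces the figure exactly. That is consistent with adding 20% to 25. The protocol shows no formula, so this is only a possible origin.

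**Step 2. Allowing for 80% adequacy.**
- Number needed for an expected 25: 25 / 0.80 = 31.25, rounded up to 32 (expected yield 32 x 0.80 = 25.6).
- Expected yield of the stated number: 30 x 0.80 = 24.
- Expected members of a 20% subset among 24: 24 x 0.20 = 4.8, against the minimum of 5.
- Subset share with 5 expected members among 24: 5 / 24 = 20.8%.
- Adequacy at which 30 would be enough: 25 / 30 = 83.3%.

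**Step 3. Chance of reaching 25.** Assume that subjects are independent and that each gives an adequate sample with probability 0.80.

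| Bronchoscopies per group | Expected adequate | P(at least 25 adequate) |
|---|---|---|
| 30 | 24.0 | 0.43 |
| 32 | 25.6 | 0.70 |

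**Step 4. Effect on the purpose of the number.** What matters is whether a true 20% subset has at least 5 members among the adequate samples. If adequacy is unrelated to subset membership, each bronchoscopied subject is an adequate subset member with probability 0.80 x 0.20 = 0.16.

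| Situation | Distribution | P(at least 5 members) |
|---|---|---|
| 30 bronchoscopies | Binomial(30, 0.16) | 0.54 |
| 32 bronchoscopies | Binomial(32, 0.16) | 0.60 |
| exactly 24 adequate samples | Binomial(24, 0.20) | 0.54 |
| exactly 25 adequate samples | Binomial(25, 0.20) | 0.58 |

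**Step 5. Does another section make up the gap?** Sections 3 and 8.2 stop at 30. Section 5 says approximately 30 of the 50 subjects in each asthma class, but all healthy subjects undergo bronchoscopy and only about 30 are enrolled, so that group has no reserve. The first interim analysis in Section 9.3 can end bronchoscopy sampling but has no rule for adding procedures. Nothing restores the missing sample.

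**The case against.** The strongest reply is that the study is exploratory. Section 9.2 itself says that no formal power calculation was done, and Section 9 says that no formal hypothesis will be tested. The rule of 5 divided by 20% is a rule of thumb about an average: even with all 25 adequate samples, a true 20% subset has 5 or more members with probability only 0.58. Section 5 uses 30 as an approximate figure. Section 9.3 plans to look for subsets across cohorts as well as within them, so the analysis is not confined to single groups of about 24.

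All of this stands, and it makes the point a minor one. It does not make the sentence correct: 31.25 does not round to 30, and the section presents 30 as the number needed under its stated assumptions.

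Three stronger readings are tempting, and the document does not support them.

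- A reader might infer that all four groups will fall short of 25. The shortfall is one sample per group in expectation. Each group misses 25 with probability 1 - 0.43 = 0.57. If groups are independent, all four miss with probability 0.57^4, about 0.11, and at least one reaches 25 with probability about 0.89.
- A reader might take the contrast of 0.43 and 0.70 as the loss in ability to find a subset. It measures only whether a count crosses 25. On the question of 5 subset members, the contrast is 0.54 and 0.60.
- A reader might state as fact that 20% was added where division by 0.80 was needed. The match with 25 x 1.2 is exact, but rounding 31.25 to a convenient figure is also possible.

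**Conclusion.** The point holds as a minor arithmetic correction. At the protocol's own 80% adequacy, 30 bronchoscopies per group are expected to give 24 adequate samples against a requirement of 25, and no other section closes the gap. The expected values need only the figures in Section 9.2. The probabilities also assume independent subjects and, for subset counts, adequacy unrelated to subset membership.

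The loss is one expected sample per group and about 0.06 (0.60 - 0.54) in the chance of seeing 5 members of a 20% subset. That does not undermine the study or call for more procedures.

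**What to change.** Correct the last sentence of the derivation in Section 9.2 in one of two ways, keeping 30 bronchoscopies per group:

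- state that 30 bronchoscopies per group are expected to give 24 adequate samples at 80% adequacy, so that the smallest subset expected to have 5 members is 20.8% (5/24); or
- state that 25 adequate samples from 30 bronchoscopies requires 83.3% adequacy.

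Either is an edit to one passage, with no extra subjects or procedures. The cost is a slightly less favourable subset size or a slightly more demanding adequacy assumption.

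Keeping both 25 and 80% would instead mean 32 per group, or 128 bronchoscopies against 120. Because every healthy subject undergoes bronchoscopy, that would raise healthy enrolment from 30 to 32 and the total from 180 to 182. It would also need changes in the Synopsis and in Sections 3, 4.1, 5, 8.2 and 9.2. The small gain in Step 4 does not seem to justify this.
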